## 3.11 Project Timeframe

| **Activity/Time** | **Month 0** | **Month 1-3** | **Month 4-6** | **Month 7-9** | **Month 10-12** |
| --- | --- | --- | --- | --- | --- |
| Ethical approval | ***** |  |  |  |  |
| Designing the intervention. |  |  |  |  |  |
| Training of CHV and research assistants |  |  |  |  |  |
| Screening and Recruitment of participants and Baseline assessments. |  |  |  |  |  |
| Baseline data analysis |  |  |  |  |  |
| Intervention and follow-up |  |  |  |  |  |
| End line data collection |  |  |  | **Month 9** |  |
| Acceptability qualitative data collection |  |  |  |  | **Month 10** |
| Data analysis and manuscript Writing |  |  |  |  |  |
| Dissemination of results  *(community, health workers and county department of health, conference, seminars, manuscript)* |  |  |  |  |  |

# APPENDIX 2: SURVEY QUESTIONNAIRE

## An adapted WHO stepwise questionnaire to collect prevalence of cardiometabolic risk factors among low income population in Kiambu County.

|  | Phone Number |  |
| --- | --- | --- |
|  | **Demographic Data** | |
|  | Age |  |
|  | Gender | 1. Male 2. Female |
|  | Highest Level Of Education | 1.Never been to school  2.Primary  3.Secondary  4.University/college  5.Other (specify |
|  | Marital status | 1.Single  2.Married  3.Divorced/separated/widowed  4.other (specify) |
|  | Work status over the past 12 months | 1. Employed  2. Self-employed  3. Homemaker  4. Retired  5. Farmer  6.Student  7. Others |
|  | Average earnings of the household for the past 1 year | ---------------------- per day  ----------------------per week  ---------------------per month |
|  | **Behavioural Measurements** | |
|  | Use of Tobacco |  |
|  | Do you use any **tobacco products** i..e cigarettes, cigars or pipes? | 1YES  2 NO |
|  | How often do you smoke cigarette? |  |
|  | At what age did you start smoking cigarette daily? |  |
|  | At what age did you **quit** smoking **daily**? |  |
|  | Do you **use** any **smokeless tobacco** *[snuff, chewing tobacco, betel]*? | 1.YES  2.NO |
|  | How often do you **use smokeless tobacco** |  |
|  | In the past 1 week has someone **in your home** smoked in your presence? | 1. YES 2. NO |
|  | In the past 1 week has someone smoked in closed areas **in your workplace** in your presence? | 1.YES  2.NO |
|  | **Alcohol Consumption** | |
|  | Have you **ever** consumed an alcohol such as beer, wine, spirits, busaa, changaa? | 1.YES  2.NO |
|  | In the past year, have you consumed alcohol? | 1.YES  2.NO |
|  | In the past 1 year how often have you consumed alcohol? | 1 Daily  2 5-6 days per week  31-4 days per week  4 1-3 days per month  5 Less than once a month |
|  | Have you taken alcohol in the past 1 month? | 1.YES  2.NO |
|  | How often have you consumed alcohol with meals | Usually with meals  Sometimes with meals  Rarely with meals  Never with meals |
|  | **Diet** | |
|  | How many days do you **eat fruit in week**? |  |
|  | How many days in a week do you **eat vegetables** |  |
|  | What type of  cooking **oil or fat is used in your household?** | 1.Vegetable oil  2.Butter or ghee  3.Margarine  4. None used  5.Other |
|  | How many meals per week do you eat outside your home |  |
|  | **Physical activity ( IPAQ)**  The questions will ask you about the time you spent being physically active in the last 7 days. Please answer each question even if you do not consider yourself to be an active person. Please think about the activities you do at work, as part of your house and yard work, to get from place to place, and in your spare time for recreation, exercise or sport. | |
|  | Think about all the vigorous activities that you did in the last 7 days. Vigorous physical activities refer to activities that take hard physical effort and make you breathe much harder than normal. Think only about those physical activities that you did for at for atleast 10 minutes at a time.  During the last 7 days, on how many days did you do vigorous physical activities like heavy lifting, digging, aerobics, or fast bicycling? | 1. -------------- days per week 2. No vigorous activity (**Skip to number 3)** |
|  | How much time did you usually spend doing vigorous physical activities on one  of those days? | 1. ………… hours per day  2. ………… minutes per day  Don’t know/Not sure |
|  | Think about all the moderate activities that you did in the last 7 days. Moderate activities refer to activities that take moderate physical effort and make you breathe somewhat harder than normal. Think only about those physical activities that you did for at least 10 minutes at a time.  During the last 7 days, on how many days did you do moderate physical activities like carrying light loads, bicycling at a regular pace, or doubles tennis?  Do not include walking. | 1.--------------------days per week  2. No moderate physical activities **(Skip to question 5)** |
|  | How much time did you usually spend doing moderate physical activities on one  of those days? | 1……………hours per day  2……………. minutes per day  3.Don’t know/Not sure |
|  | Think about the time you spent walking in the last 7 days. This includes at work and at home, walking to travel from place to place, and any other walking that you have done solely for recreation, sport, exercise, or leisure.  During the last 7 days, on how many days did you walk for at least 10 minutes  at a time? | 1.……………. days per week  2.No walking Skip to question 7 |
|  | *The last question is about the time you spent sitting on weekdays during the last 7 days. Include time spent at work, at home, while doing course work and during leisure time. This may include time spent sitting at a desk, visiting friends, reading, or sitting or lying down to watch television*.  During the last 7 days, how much time did you spend sitting on a week day? | 1.…………… hours per day  2……………. minutes per day  Don’t know/Not sure |
| **History of Raised Blood Pressure** | | |
|  | Have you ever had your blood pressure measured? |  |
|  | Have you ever been told by a doctor or other health worker that you have raised blood pressure or hypertension? |  |
|  | Are you on any treatments/advice for high blood pressure? | |
|  | Drugs (medication) that you have taken in the past two weeks |  |
|  | Advice to reduce salt intake |  |
|  | Advice or treatment to stop smoking |  |
|  | Advice to start or do more exercise |  |
| **Step 2 Physical Measurements** | | |
|  | Interviewer ID |  |
|  | Device IDs for height and weight |  |
|  | Height(cm) |  |
|  | Weight(kg) |  |
|  | **For women:** Are you pregnant? |  |
|  | Waist circumference(cm) |  |

# APPENDIX 3: CLIENT SATISFACTION QUESTIONNAIRE.

1. What is your take on the use of CHW intervention for managing Blood pressure

Satisfactory ( )

Neutral ( )

Not satisfactory ( )

If satisfactory why

If unsatisfactory, why

1. Would you liketo continue with the CHW lifestyle intervention ?

Yes ( ) No ( )

If no, why

1. Would you recommend that other patients be supported by CHW in the management of blood pressure through lifestyle intervention?

Yes ( ) No ( )

If no, why

1. Do you have any complain(s) in regard to this method of being supported by CHW in the management of blood pressure through lifestyle intervention?

Yes ( ) No ( )

If yes:-

What were the complains

1. Do you any commendation(s) in regard to this method of being supported by CHW in the management of blood pressure through lifestyle intervention?

Yes ( ) No ( )

If yes: -

1. What were the commendations
2. What was the reaction of most of the other family members towards you being supported by CHW in the management of blood pressure through lifestyle intervention?

Positive( )

Negative ( )

1. What was the reaction of most of the other community members about hypertensive patients supported by CHW in the management of blood pressure through lifestyle intervention?

Positive ( )

Negative ( )

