## 2.3 Specific Objectives

i. To determine the prevalence of hypertension among adults in selected wards in Kiambu County.

ii. To determine the baseline cardio-metabolic risk among hypertensive patients in Kiambu County.

iii. To determine the effectiveness of a multicomponent CHW lifestyle intervention for control of BP among hypertensive patients in Kiambu County.

iv. To determine the acceptability of a multicomponent CHW lifestyle intervention for control of blood pressure among hypertensive patients in Kiambu County.

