## 3.4 Sample size and power calculation

With changes in BP as the primary outcome we calculated a sample of 52 between the 2 groups to show changes in BP between the intervention and control groups at a significance level of 0.05 for a two-sided test with 80% statistical power of finding a large effect (*Cohen’s d*=0.80). This study will be underpowered to find significantly small effect (*Cohen’s d*=0.30) and moderate effect (*Cohen’s d*=0.50), however, we will be able to calculate an effect size and the direction of its impact.

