## 3.7 Data for feasibility and acceptability assessment

At the end of the study, participants in the intervention arm will complete the Client Satisfaction Questionnaire(Larsen et al., 1979) to assess acceptability of the CHW intervention. In addition, 10 patients (purposively sampled to include both gender and different age groups) and CHWs from the intervention group will be targeted for in-depth interviews (IDIs) to understand their experiences and perceptions on the utility of the intervention in the control of hypertension. The IDI guide will cover questions on experiences from using the intervention and determinants of its use. We will assess feasibility of the intervention by examining recruitment rates, follow-up home visits completion rate, dropouts, and adherence to the individualized physical activity program.

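### The family and community items in Appendix 3 offer only Positive or Negative, so a patient with no reaction to report must tick an ill-fitting box or leave an unexplained blank

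*Protocol*

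**What the plan says.** Section 2.3 of the protocol sets as its fourth specific objective "To determine the acceptability of a multicomponent CHW lifestyle intervention for control of blood pressure". Section 3.7 names the instrument: at the end of the study, "participants in the intervention arm will complete the Client Satisfaction Questionnaire". It adds in-depth interviews with 10 purposively chosen patients and with CHWs from the intervention group, "to understand their experiences and perceptions on the utility of the intervention in the control of hypertension".

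Appendix 3 prints the form. It has seven closed items: overall view, wish to continue, would recommend, complaints, commendations, family reaction and community reaction. (The printed numbering is broken; the question on what the commendations were is the follow-up to the fifth item.) The last two are:

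- family: "What was the reaction of most of the other family members towards you being supported by CHW in the management of blood pressure"
- community: "What was the reaction of most of the other community members about hypertensive patients supported by CHW in the management of blood pressure"

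Each gives two boxes, Positive and Negative, and nothing else. The protocol does not require every item to be answered, says nothing about blanks, and names no endpoint or analysis for these two items.

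**The concern.** The two boxes do not cover the possible answers. Some patients will have seen no reaction from others or will not know of one, and some will have no relatives who know about the visits. None of these is Positive or Negative. Such a patient either picks a box that misdescribes the situation or leaves the item empty, and the form does not show which happened or why.

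These are the only questionnaire items on how family and community received a programme delivered in the home. The protocol also intends the acceptability data to inform a later, fully powered trial (section 1.2). If a tick for Positive can mean either approval or that nobody said anything, the percentage is hard to use for that purpose. The response options are fixed in the protocol's own form, so no later analysis can recover a category that was never collected.

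**Working it through.** **Step 1: compare the response options across the protocol's forms.**

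| Item | Options | Follow-up |
|---|---|---|
| Appendix 3, overall view | Satisfactory / Neutral / Not satisfactory | Reasons asked |
| Appendix 3, continue; recommend | Yes / No | Reason asked if No |
| Appendix 3, complaints; commendations | Yes / No | Content asked if Yes |
| Appendix 3, family; community | Positive / Negative | None |
| Appendix 2, IPAQ vigorous, moderate and sitting time | Hours or minutes, or "Don’t know/Not sure" | Not applicable |

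The investigators use a middle category and a don't-know option elsewhere. Both are absent from the two items that ask a patient to report what other people thought, which are also the only two without a follow-up.

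**Step 2: could the gap be filled from other data?** The Appendix 2 questionnaire records marital status, but not household size, living alone or whether the condition has been disclosed. A blank cannot be sorted into no family, not told, or skipped.

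**Step 3: illustrate the size.** The protocol gives no figure on this point, so nothing can be reproduced and the inputs are assumptions:

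- m = 26 patients answering. Section 3.4 says "we calculated a sample of 52 between the 2 groups", and 52/2 = 26. This assumes 1:1 allocation, which is not stated, and no dropout.
- p = 13 patients who truly saw a positive reaction (assumed).
- k = 5 to 10 patients with no reaction to report (assumed).

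The sensible target is the positive share among those who saw a reaction, p/(m − k):

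- k = 5: 13/21 = 61.9%
- k = 10: 13/16 = 81.3%

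What the printed form would show:

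| The k patients | Formula | k = 5 | k = 10 |
|---|---|---|---|
| all tick Positive | (p + k)/m | 18/26 = 69.2% | 23/26 = 88.5% |
| all tick Negative | p/m | 13/26 = 50.0% | 13/26 = 50.0% |
| all leave blank, blanks excluded | p/(m − k) | 61.9% | 81.3% |

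Difference from the target:

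- all Positive: 69.2 − 61.9 = +7.3 points; 88.5 − 81.3 = +7.2 points
- all Negative: 50.0 − 61.9 = −11.9 points; 50.0 − 81.3 = −31.3 points
- all blank and excluded: 0

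**Step 4: vary the assumption.** Take 80% positive among those with a reaction and k = 5. The form then shows (0.8 × 21 + 5)/26 = 83.8% if all five tick Positive, (0.8 × 21)/26 = 64.6% if all tick Negative, and 80.0% if all leave it blank and blanks are excluded. The sign of the error again depends on how the unsuited patients answer.

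**The case against.** Several arguments limit the point, and most of them stand.

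- *Blanks are allowed.* A reader might infer that every such patient must be recorded as Positive or Negative, so that acceptance is certain to be misstated. The protocol does not support this: no rule requires an answer, and a blank is a missing value rather than a wrong one. What remains is that the blank carries no reason.
- *The direction is not shown.* One might expect patients who stayed to the end to favour Positive, so that acceptability is overstated. Nothing in the protocol shows this, and the working gives errors of either sign.
- *A large figure is tempting.* Setting 69-88% against 13/26 = 50% suggests an overstatement of 19 to 38 points. That comparison counts patients with no reaction as not positive. Against the share among those with a reaction, the gap is about 7 points.
- *The community item is broader than the respondent.* It asks about CHW-supported hypertensive patients in general, so a patient who has not disclosed the condition may still be able to answer. Section 3.5 also has CHWs screening door to door, so their work is visible locally. Likewise, the family item concerns family members, not household members, so living alone does not make it unanswerable. Both items ask about most others, which largely deals with mixed reactions. Not having seen a reaction, or not knowing, remains uncovered in both.
- *Two-option answers are common on this form.* Six of the seven items have them. But the Yes/No items ask for the patient's own wish, recommendation or comment, each with a follow-up. The last two ask for knowledge of other people and have no follow-up.
- *Other sources exist.* The first three items measure acceptability to the patient directly, and the interviews leave room for absent or indifferent reactions. This stands, although 10 purposively chosen patients cannot supply a proportion for the arm.

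**Conclusion.** The defect is real and small. Two of the seven closed items lack any option for no reaction, not aware or not applicable, and their positive share may be distorted upwards or downwards. The protocol does not allow the size to be determined. Under the assumed 26 respondents, 13 truly positive and 5 to 10 without a reaction, the overstatement is about 7 points if all of the latter tick Positive. The share is too low if they tick Negative, and unbiased if they leave the item blank and blanks are excluded.

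A reader might go further and conclude that objective iv fails. The protocol does not support that: no family or community acceptance endpoint or threshold is named, the items are descriptive and confined to one arm, and acceptability has other sources. Blood pressure outcomes and the randomised comparison are not affected. This is a low-severity improvement to a form.

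**What to change.** Before Appendix 3 is used, add two options to both the family and the community item: *Neutral / no reaction* and *Not aware / not applicable*. Report the percentage positive among patients who saw a reaction, with its denominator, and next to it the counts in the two added categories and the count of blanks.

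The cost is two extra tick boxes on each of two items and one more line in a table, with no additional visit or staff. The main percentage will rest on a smaller denominator: in the illustration, 16 to 21 patients instead of 26.

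The change must come before data collection, because the missing category cannot be reconstructed afterwards.
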